5.4 Co-interventions

After the clinically successful intervention on the bile duct (decrease of the bilirubin value), palliative chemotherapy can be performed depending on the underlying malignant disease. The respective chemotherapy is specified in the documentation. Palliative chemotherapy can influence the rate of reintervention (usually reduction of the rate of reintervention), disease-specific survival (usually prolongation) and overall survival (usually prolongation). This is taken into account in the evaluation of the data.

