6.4 Control visits

On the day after the technically successful intervention, the patient's pain sensation is recorded by means of a visual analogue scale (0-10) (Case Report Form; Control Visit No.1, p.5).

The next visit is on day 7 after the technically successful intervention (Case Report Form; Control Visit No.2, p.6). If a re-intervention is necessary (see Chapter 2.1), the count is only made from the day of successful intervention (metal stent implantation). If the patient is discharged from the hospital within the seven days after technically successful intervention, it must be ensured that the attending general practitioner carries out the laboratory check and the result is obtained from the general practitioner. The determination of bilirubin has been so standardized for many years that no central laboratory is necessary. In addition, the intensity of pain according to the visual analogue scale (0-10) must be obtained from the investigating physician or his representative by telephone or post on day 7 after a technically successful intervention. Adverse events and re-interventions, including the patient's discharge day (which is counted), are documented to determine the length of hospital stay in days.

The patient is called to a staging by means of CT or MRI abdomen after three (no data collection here) and six months of the technically successful intervention as an outpatient or inpatient (not study related). The date six months after intervention should be used for a detailed study visit. Previously undocumented complications in a 30-day interval and reinterventions within the six months after the intervention will be documented (Case Report Form; Control Visit No. 3, pp.7-8). If the patient is not examined at the trial centre, it must be ensured that the relevant data on re-interventions or complications can be obtained by calling the family doctor or patient.

If the patient should be referred to tumor therapy (palliative chemotherapy, immunotherapy, antibody therapy) as part of the malignant underlying disease, this will be documented with "yes/no" and the therapy will be named. It can be assumed that a tumor therapy has a positive influence on the re-intervention rate as well as on the disease-specific survival and overall survival.

Data documented in the study

Control visit no.1 (1 day after intervention)

Intensity of pain on the visual analogue scale (0-10) Complication(s) since intervention (yes/no)

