Serious adverse events (SUE) since intervention (yes/no)

Control visit no.2 (7 days after technically successful intervention

Intensity of pain on the visual analogue scale (0-10) Date Bilirubin determination (after initial intervention)

Laboratory chemical result of the bilirubin determination (after initial intervention, in mg/dl)

Duration of hospital stay from day of intervention (inclusive) to day of discharge (date of hospital discharge, if later than 7 days, please add later!)

Re-intervention(s) since control visit 1 (yes/no) Complication(s) since control visit 1 (yes/no)

Serious adverse events (SUE) since intervention (yes/no)

Control visit no.3 (6 months after intervention) and/or study completion visit

The final study visit coincides with the follow-up visit after six months. To calculate the Overall Survival or Disease Specific Survival, it is noted whether the patient is still alive or when he/she died and why (date of death, calculation of survival time in days, cause of death). If the patient is not examined at the trial centre or has died in the meantime, it must be ensured that the relevant data on re-intervention, adverse events, date of death and cause of death can be obtained by calling the family doctor or relatives.

Data that are documented within the framework of the study:

Date of end of study/last contact

Reason for termination:

- Regular termination of the study (yes/no)

- Patient has died (yes/no)

Date of death

Cause of death on the ground of the underlying malignant disease (yes/no)

Cause of death other than underlying malignant disease (yes/no)

Cause of death unclear (yes/no)

Revocation of consent (yes/no)

Patient no longer appeared/follow-up data no longer to be collected (yes/no)

Intervention not successful, no new attempt

Other (specification)

Chemotherapy carried out during the course (yes/no)

Chemotherapy protocol (name): first line/second line/third line (multiple answers possible)

- Gemcitabine mono (yes/no)

- Gemcitabine/Nab-paclitaxel (yes/no)

- FOLFIRINOX (yes/no)

- Cisplatin/Gemcitabine (yes/no)

- FLO (T) (yes/no)

- FOLFIRI (yes/no)

- Paclitaxel/Ramucirumab (yes/no)

- Ramucirumab mono (yes/no)

- 5 FU mono (yes/no)

- Other chemotherapy/immunotherapy (yes/no)

Other therapy (but no chemotherapy) performed (yes/no)

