9.1 Case Number Calculation

The calculation of the number of cases refers to the primary endpoint, the technical success rate. In the literature, rates of approximately 95% are given in similar studies (Lee et al. (2016)). This is assumed for both groups. If the technical success rate in the PTBD group is less than 10% lower than in the EUCD group, it is considered clinically irrelevant based on clinical judgment. Therefore, the non-inferiority threshold is defined as δ=0.1. At a unilateral significance level of 2.5%, 200 patients (100 per group) are required to perform a Farrington/Manning test at 80% power (calculations with PASS 14.0.8). It is assumed that for a very small proportion of patients the primary endpoint will not be met (for example, if a complication leads to premature discontinuation of the intervention). Therefore, at least 106 patients per group should be included to compensate for a loss of information due to 5% assumed drop-outs.

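### Chemotherapy after drainage is to be taken into account for re-intervention and survival, but no start date is listed, so a fixed ever/never adjustment would be biased and no valid time-dependent or landmark analysis could replace it

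*Protocol*

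**What the plan says.** Section 5.4 places chemotherapy after the procedure and makes it depend on the procedure's result: "After the clinically successful intervention on the bile duct (decrease of the bilirubin value), palliative chemotherapy can be performed depending on the underlying malignant disease". It names the re-intervention rate, disease-specific survival (DSS) and overall survival (OS) as outcomes that chemotherapy can change, and closes with "This is taken into account in the evaluation of the data". No method is given. Section 6.4 repeats the expected direction for re-intervention, DSS and OS: "It can be assumed that a tumor therapy has a positive influence on the re-intervention rate as well as on the disease-specific survival and overall" (quoted without its last word).

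The data items for control visit no. 3 in section 6.4 are "Chemotherapy carried out during the course (yes/no"), the regimen by name, and the line of therapy. Dates are listed for death, bilirubin determination, discharge and last contact, but not for chemotherapy.

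Sections 7.2.3 and 7.2.4 start the survival clock at the beginning of the intervention. Section 2 makes clinical success (bilirubin fall of at least 50% at day 7) the first secondary endpoint. In section 9.2 the only outcome named for the regression models is technical success, and the inputs named are intervention, BMI and bilirubin. Apart from the hierarchical test of complications, secondary endpoints are descriptive, with descriptive p-values and 95% confidence intervals.

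**The concern.** Chemotherapy is not a baseline characteristic here. A patient becomes a yes only by draining well enough and living long enough to start, and everyone who dies early is a no. Two problems follow if that status is treated as if it were known at time zero.

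- **Immortal time.** The interval from intervention to first chemotherapy is free of deaths, by construction, in the yes group. Chemotherapy then looks protective even if it does nothing.
- **Conditioning on a consequence of the procedure.** If one method drains better and so gives more patients access to chemotherapy, adjusting for chemotherapy removes part of that method's effect and also brings in the immortal-time distortion.

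Unequal access is plausible. The study is non-randomised with one method per centre (sections 4.2 and 5.3), so local oncology practice is tied to arm, and section 1.1 cites a meta-analysis reporting lower clinical success with PTBD. At stake are the comparisons of re-intervention and survival. Section 1.2 intends re-intervention, among other results, to inform which method should be preferred.

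**Working it through.** **1. The plan's own figure.** The only sample-size figure concerns technical success, in section 9.1: "At a unilateral significance level of 2.5%, 200 patients (100 per group) are required to perform a Farrington/Manning test at 80% power", with "rates of approximately 95% are given in similar studies" assumed for both arms and a margin where "the non-inferiority threshold is defined as δ=0.1". The restricted estimates under the null are 0.9703 (EUCD) and 0.8703 (PTBD).

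- s0 = √(0.9703×0.0297 + 0.8703×0.1297) = 0.3764; s1 = √(2×0.95×0.05) = 0.3082
- n = [(1.960×0.3764 + 0.8416×0.3082)/0.10]² = 99.4, so 100 per group
- 100/0.95 = 105.3, so 106, as in "at least 106 patients per group should be included to compensate for a loss of information due to 5% assumed drop-outs"

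The figure reproduces. Chemotherapy plays no part in it.

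**2. Can the bias be avoided with the listed items?** A time-dependent covariate needs the day on which each patient changes from untreated to treated. A landmark analysis needs to know whether treatment had started by the landmark day. Yes/no, regimen and line supply neither. Section 7 refers to chapter 6 for the data collected, and section 10.1 says the CRFs follow the protocol. Any adjustment or stratification from these items would therefore rest on undated status.

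**3. Size of the immortal-time effect.** The protocol gives no survival, uptake or timing figures, so all inputs in steps 3 and 4 are assumptions. A single case shows the mechanism. With exponential survival, median 150 days, and chemotherapy due on day 49 (7 + 42), the chance of dying before it starts is 1 − 0.5^(49/150) = 0.20. One in five patients who were due chemotherapy is then counted as never treated, and all of them are early deaths.

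The model is λ(t) = λ0(t)·exp(βA·arm + βC·ever), with survival censored at six months and **no true chemotherapy effect** (hazard ratio, HR, 1.0):

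| Assumptions | Apparent chemotherapy HR | Arm HR |
|---|---|---|
| 60% planned, start at 0.5-2 months, median survival 3, 4, 6 months (no arm term) | 0.50, 0.53, 0.53 | not applicable |
| 90% clinical success in both arms, start after day 7 with median delay 21-84 days, median survival 90-240 days | 0.27-0.35 | 0.97-1.01, with or without adjustment |

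**4. Size of the arm distortion when access differs.** True chemotherapy HR 0.6; the arm effect acts only through access to chemotherapy:

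| Assumptions | Arm HR unadjusted | Arm HR adjusted for ever/never |
|---|---|---|
| Clinical success 90% v 70%, delay 21-42 days; HR for the better-draining arm | 0.90-0.96 | 1.25-1.36 |
| 70% v 50% planned for chemotherapy; HR for the worse-draining arm | 1.09 | 0.89 |

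The direction reverses in both. Re-intervention was not simulated. The same conditioning problem applies to it, but no size is claimed.

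**The case against.** A reader might infer that the protocol prescribes a biased adjustment. It does not. Section 5.4 names no method, section 9.2 does not list chemotherapy among its regression inputs, and the phrase could mean a descriptive display, cautious interpretation, or a method set out in the analysis plan. This stands, and the point is therefore conditional. It does not dispose of the concern, because an analysis plan can choose a method but cannot supply a date that was not collected.

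A reader might also infer that chemotherapy is recorded only as yes/no. That is wrong, since regimen and line are recorded too. What is absent from the list is the date. The CRF and the visit figure are not available, so a date field there cannot be excluded.

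Chemotherapy is not purely a consequence of arm. Section 5.4 also makes it depend on the malignant disease, so it may partly mark case mix or centre practice. This is fair, but undated post-procedure status is a poor tool for that purpose. Case mix is better handled through baseline items such as the cause of obstruction in section 6.2.

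Finally, section 1.3 expects similar success in both arms, and a study of 212 patients is noisy. Even if all 212 died, the standard error of the log HR would be about 2/√212 = 0.137. A 95% interval around 1.09 would then be 1.09 ÷ and × exp(1.96×0.137), or 0.83 to 1.43, which contains 0.89. This stands as a limit on what one trial could demonstrate. It does not remove the bias: ln(0.89/1.09) = −0.20 is a systematic shift of about 1.5 such standard errors.

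**Conclusion.** The concern holds in conditional form. The protocol promises to account for a variable that arises after the procedure, depends on an endpoint compared between arms, and has no listed start date. A fixed ever/never covariate or stratum would give a spuriously protective chemotherapy effect (about 0.27 to 0.53 under the assumed inputs when the truth is 1.0). It would distort the PTBD-EUCD comparison only if access to or timing of chemotherapy differs between arms. With equal access the arm HR stays near 1.0.

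The sizes are illustrative. They depend on assumed exponential survival, uptake and timing, and the reversal of the arm effect depends on assumed unequal access. Neither a reversal in this trial nor its direction can be predicted from the protocol.

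It would also be wrong to infer that the main conclusion is at risk. The non-inferiority test, its 106 patients per group and the hierarchical complication test are untouched. The affected results are secondary and descriptive. The change is still worth making, because dates are easy to collect prospectively and hard to recover after patients have died.

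**What to change.** - **Sections 6.4 and CRF:** add the start date of the first tumour therapy given after the intervention.
- **Sections 5.4 and 9.2:** replace the open promise with a statement that the main arm comparisons of re-intervention, OS and DSS are neither adjusted for nor stratified by chemotherapy given after the procedure.
- **Reporting:** describe chemotherapy use and time to start per arm, as something that happens after the procedure.
- **Any analysis of its role:** label it exploratory, and enter chemotherapy as a time-dependent covariate or use a landmark day fixed in advance.

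The cost is one additional date at the six-month visit and a short text change. Sample size and the primary analysis stay as they are.

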5.5 Re-interventions

Re-interventions are defined as renewed or repeated performance of PTBD or EUCD. Re-interventions may become necessary to complete a technically successful implantation of a metal stent in the bile duct. This may be the case, for example, if in the case of PTBD only the creation of an external drainage (drainage to the outside, no overcoming of the tumor stenosis) was possible in the first intervention. Planned re-interventions are avoided within the study concept (e.g. leaving the external/internal drainage after technically successful PTBD with stent implantation and radiological control of the result on the following day). After technically successful implantation of the metal stent, stent closure, stent migration (change of position) or other stent malfunction may occur in the further course (following months). This is usually clinically visible by an increase in the laboratory chemical parameters for bile duct occlusion (increase in bilirubin, increase in alkaline phosphatase) or by cholangitis (additional signs of infection). Any Re-intervention on the bile duct that is related to the primary method used, PTBD or EUCD, is considered as re-intervention in the documentation of the data. Thus, an operation (for example: creation of a biliodigestive anastomosis) which becomes necessary as a result of the "malfunction" of the metal stent is also counted as a re-intervention (!).

5.6 Pre- and concomitant diseases

Pre- and concomitant diseases besides the underlying malignant disease that are present at the time of informed consent are not documented, as they are not expected to have a relevant impact on key endpoints of the study such as the technical and/or clinical success rate or the occurrence of complications of the intervention. By differentiating between Overall Survival and Disease Specific Survival, it is possible to specify the proportion of disease-specific causes (related to the underlying malignant disease causing the biliary obstruction) in the death of patients. It is expected that the underlying malignant disease is the main life-limiting factor in the observation period.

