**3. STUDY CONCEPTION/ DESIGN**

3.1 Study design

Prospective, multicentre, non-randomized, open, confirmatory, 2-arm non-inferiority study in parallel group design

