4.2 Trial centres

The present study is conducted multicentre (5 centres PTBD, 5 centres EUCD).

Due to the complexity of the interventions, only one of the two interventions is carried out in each centre, namely the one that is also carried out there by default.

When selecting the centres for the study, care is taken to ensure that the same number of centres participate for both intervention groups.

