5.3 Randomisation and blinding

Randomisation is not carried out, as one centre cannot usually offer both interventions (PTBD and EUCD) of the same high quality due to the complexity and experience required. Therefore, each centre offers the respective standard method (EUCD or PTBD). At least 10 study centres will participate in the study. When selecting the centres, care is taken to ensure that both university hospitals and non-university institutions are selected for both groups. All potentially eligible patients will be screened (see Chapter 6.1) and, if suitable, informed about the study. It is assumed that the recruited patients of both groups have similar characteristics and are comparable. Possible differences in patient characteristics are taken into account in the data evaluation. However, it is not expected that different patient characteristics (e.g. pancreatic carcinoma and bile duct obstruction versus LK metastasis in liver hilus with bile duct obstruction) will have a relevant influence on the success or failure of the intervention.

Due to the nature of the interventions, the attending physician cannot be blinded. Since only one of the two surgical techniques is used in a centre, the patient and study nurses cannot be blinded either. With the exception of the secondary endpoint of pain perception, the endpoints, especially the primary endpoint, are objectively measurable outcomes. Therefore, it is assumed here that there is little room for influence and that the risk of bias is low. The biometrician has no access to the data until after the database has been closed.

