6.2 Baseline visit

Facts of the clinical picture are documented (Case Report Form,p.3) . Cause of malignant bile duct obstruction, date of first diagnosis of the malignant underlying disease, cause of unsuccessful or for anatomical reasons not feasible ERCP.

The bilirubin value in mg/dl as an expression of the bile duct obstruction or cholestasis is measured and noted. The baseline visit should be performed the day before the intervention. Depending on the timing within the centre, baseline visit can be on the same day as screening visit if the intervention is scheduled for the following day.

Data that are documented as part of the study:

Demographics

- Gender

- Age

- Size

- Weight

Cause of the malignant bile duct obstruction (no multiple answers)

- Pancreatic carcinoma

- Distal bile duct carcinoma or extrahepatic bile duct carcinoma (Bismuth I)

- Gall bladder carcinoma

- Stomach cancer

- Duodenal carcinoma

- Papillary carcinoma

- Metastasis of another malign disease

- Other cause

Date of first diagnosis of the underlying malignant disease

Cause of unsuccessful or for anatomical reasons not feasible ERCP (no multiple answers)

- Gastric outlet stenosis/duodenal stenosis (tumour-related or benign cause)

- Difficult to probe the optic disc using ERCP

- For (partial) gastrectomy

- Biliodigestive anastomosis

- Following bariatric surgery

- Other cause

Laboratory chemical result of bilirubin determination (in g/dl) Pain intensity on the visual analogue scale (0-10)

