9.2 Statistical evaluation

The primary endpoint is the technical success rate in malignant distal choledochial stenosis using a self-expanding metal stent. The non-inferiority of PTBD compared to EUCD shall be demonstrated. The corresponding test hypothesis is

H0: pEUCD - pPTBD ≥ δ vs. H1: pEUCD - pPTBD < δ

Where pPTBD describes the technical success rate in the EUCD group, pPTBD the technical success rate in the PTBD group and δ=0.1 the non-inferiority limit.

The non-inferiority of PTBD to EUCD is verified by the Farrington/Manning test with a one-sided significance level of 2.5%.

Since this is a non-inferiority study, the primary evaluation will be based on both the Intention-To-Treat (ITT) Set and the Per-Protocol (PP) Set. In the ITT set, all patients are considered in whom the intervention was performed, even if it was technically unsuccessful or participation in the study was terminated prematurely. If the intervention has to be terminated prematurely (e.g. due to organ perforation), this patient is included in the primary evaluation. The primary evaluation is based on the assumption of technical failure in these patients.

In the PP Set, only those patients are included in the evaluation for whom the intervention was performed and the technical success was measured.

In sensitivity analyses, best case and worst case scenarios are calculated for the missing values. In addition, regression models are planned to investigate the influence of confounders on the endpoints. The variables intervention (EUCD with subgroups or PTBD with side localisation), BMI or bilirubin value are considered as input variables in the baseline study. The binary outcome variable is the technical success of the intervention. The affiliation of the individual patients to the two evaluation collectives is defined in SAP before the database is closed.

If non-inferiority can be shown with regard to the technical success rate, the occurrence of at least one complication (expected complication rate for both interventions: 10-20%) is compared hierarchically in the next step and tested for differences between the groups (based on the ITT set). Due to the hierarchical approach, the full level alpha, in this case two-sided 5%, is tested.

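### Comorbidity is by rule not recorded in a trial where the centre fixes the arm, so the confirmatory complication test cannot be adjusted, or checked for imbalance, on comorbidity or general condition

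*Protocol*

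**What the plan says.** Section 3.1 describes the trial as a "Prospective, multicentre, non-randomized, open, confirmatory, 2-arm non-inferiority study in parallel group design". Under section 4.2, "only one of the two interventions is carried out in each centre", so the arm follows from where a patient is treated.

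Section 5.3 assumes that the two groups will be comparable and adds: "Possible differences in patient characteristics are taken into account in the data evaluation". Section 5.6 then says that pre-existing and concomitant diseases other than the malignancy "are not documented, as they are not expected to have a relevant impact on key endpoints of the study", naming technical success, clinical success and complications. It adds that separating disease-specific from overall survival will show how many deaths are due to the tumour.

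Section 6.2, under "Data that are documented as part of the study", lists sex, age, height, weight, cause of obstruction, date of first diagnosis, reason for ERCP failure, bilirubin and pain. It lists no comorbidity, performance status, ASA class, ascites or disease-extent item.

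Section 9.2 plans regression models for confounders. Besides the intervention, "BMI or bilirubin value are considered as input variables in the baseline study", and "The binary outcome variable is the technical success of the intervention". If non-inferiority is shown, complications are tested next, hierarchically, at two-sided 5%. By section 2 that endpoint includes death within 30 days.

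**The concern.** Without randomisation, a difference in case mix between PTBD and EUCD centres goes straight into the comparison. The only protection is to measure the relevant characteristics, show them by arm and adjust for them. Section 5.3 accepts this, but section 5.6 withholds one group of the data needed. Its reason, that no relevant impact is expected, is an assumption that the trial then cannot test.

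What is at stake is the second confirmatory test. Its listed events include bleeding and sepsis as well as death, and general condition can plausibly influence all of these. Section 1.2 says that the results may be used to restate which method should be preferred after failed ERCP. A case-mix difference could then be read as an effect of technique. A later analysis plan cannot repair this, because it can use only what the CRF holds.

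**Working it through.** **Number per arm.** Section 9.1 gives 100 per group: 95% success in both arms, margin 0.10, one-sided 2.5%, 80% power, Farrington/Manning test. Recalculation with the restricted variance gives 100 per group (power 80.3%), and 100 / (1 − 0.05) = 105.3, rounded up to 106. The plan's figure reproduces, and n = 106 per arm is used below.

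**Assumptions.** The documents give neither the prevalence nor the effect of comorbidity. Suppose that the procedures have the same true complication risk, and that an unrecorded factor raises the risk from r0 to r1 and is present in shares q1 and q2 of the two arms. The expected rate in arm i is

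p_i = r0 × (1 − q_i) + r1 × q_i.

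The test is a pooled two-proportion z test, two-sided 5%, given that the hierarchy reaches it.

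**Worked case** (r0 = 10%, r1 = 25%, shares 30% and 50%):
- p1 = 0.10 × 0.7 + 0.25 × 0.3 = 0.145
- p2 = 0.10 × 0.5 + 0.25 × 0.5 = 0.175
- Mean rate 0.16; SE0 = √(2 × 0.16 × 0.84 / 106) = 0.0504; SE1 = √((0.145 × 0.855 + 0.175 × 0.825) / 106) = 0.0503
- Rejection ≈ Φ((0.03 − 1.96 × 0.0504) / 0.0503) + Φ((−0.03 − 1.96 × 0.0504) / 0.0503) = 0.086 + 0.005 = 0.091
- Exact enumeration gives 0.092.

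**Range, by exact enumeration:**

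| r0 / r1 (risk ratio) | Shares | Expected rates | False rejection, two-sided |
|---|---|---|---|
| no imbalance | equal | 15% v 15% | 5.1% |
| 10% / 20% (2) | 30% v 40% | 13% v 14% | 5.7% |
| 10% / 25% (2.5) | 30% v 50% | 14.5% v 17.5% | 9.2% |
| 10% / 30% (3) | 25% v 55% | 15% v 21% | 20.6% |

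These rates lie within or close to the 10–20% that section 9.2 expects. A wider grid (baseline risks 8–15%, risk ratios 1.5–3, imbalances of 10–30 percentage points, normal approximation) runs from 5.1% to 32.3%. Its top value needs rates of 21% v 30%, above what section 9.2 expects.

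**What adjustment the data can carry.** Among 212 patients, complications at 10–20% give 212 × 0.10 = 21 to 212 × 0.20 = 42 events. Technical failure at 5% gives 212 × 0.05 = 10.6, about 11 events. A model with arm, age, bilirubin and four added items has at least seven parameters. That is 21 / 7 = 3 to 42 / 7 = 6 events per parameter for complications and 10.6 / 7 = 1.5 for technical success.

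**The case against.** **Scope of the refusal.** A reader might infer that the protocol deliberately declines to record general condition. Section 5.6 covers concomitant disease only. Performance status, ASA class, ascites and disease extent are merely absent from the list in 6.2, and the data overview in Figure 1 is not shown. This objection stands.

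**Partial adjustment.** A reader might also infer that nothing useful can be adjusted. Age, sex, height, weight, tumour cause, diagnosis date, reason for ERCP failure, bilirubin and later chemotherapy are recorded. The promise in 5.3 can be kept for those, and an analysis plan may name more of them than 9.2 does. What remains out of reach is comorbidity and general condition.

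**Eligibility.** Section 4.4 requires imaging to rule out advanced disease with very poor prognosis, and 4.5 excludes impaired coagulation. Both narrow the possible imbalance. However, 4.5 contains no criterion that matches the prognosis judgement, so that judgement rests with centres and may differ by arm.

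**Endpoint.** Section 8.1 lists mainly procedure-specific events, leaves out those due to sedation or chemotherapy, and counts cholangitis only if it is new and attributable to the intervention. This weakens the route from frailty to complications but does not close it, since bleeding, sepsis and death within 30 days still count.

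**Survival.** It is descriptive, and 5.6 openly relies on disease-specific survival. That helps with cause of death. It does not help the complication test, and it does not remove confounding of survival by baseline condition.

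**Centre.** Because each centre offers one method, centre and operator effects stay confounded with arm whatever is recorded. This is true, but patient case mix is the part that can be measured.

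**Conclusion.** The point holds in this form: the protocol rules out recording comorbidity and lists no measure of general condition, so the hierarchical complication test can be neither adjusted for these nor checked for imbalance in them. That undercuts section 5.3 for an important group of characteristics.

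The size is unknown. On the assumed values, the two-sided false rejection rate is near the nominal 5% under weak imbalance and about 9% to 20% with risk ratios of 2.5 to 3 and imbalances of 20 to 30 percentage points. These are illustrations and not estimates of the trial's error rate. It would be wrong to infer that the test is known to be inflated, because the documents contain nothing that shows an imbalance. The trial as planned could not tell which case applies.

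The sample size is unaffected. This should be changed, but it does not by itself invalidate the design.

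**What to change.** - **Section 5.6:** delete the rule that concomitant diseases are not documented.
- **Section 6.2 and the CRF:** add a short baseline set from the routine work-up: ASA class or one comorbidity item, performance status, ascites and liver metastases. Sections 4.4 and 6.1 already require abdominal sonography and CT or MRI, and 6.1 already provides for sedation or anaesthesia.
- **Section 9.2:** report these items by arm, and add an adjusted complication comparison as a sensitivity analysis. With 21 to 42 expected events, use a sparse model or a propensity score. The propensity model has arm as its outcome, with 106 patients on each side, so it carries several covariates more easily. Do not fit the full set for technical success, where about 11 failures are expected.

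The cost is about four CRF fields and slightly more documentation per patient. Once enrolment has begun it also needs an amendment under section 11.2, with the items taken from source records for patients already included. The change does not separate centre effects from arm, and the report should say so.
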